## **PROTOCOL SYNOPSIS:**

### **CONCEPT/RATIONALE:**

Maintaining adequate nutrition to minimize weight loss during chemoradiotherapy for head and neck cancer is crucial for treatment adherence, minimizing short- and long-term treatment-related complications, quality of life (QOL), and cancer-related outcomes. However, as chemoradiation may result significant acute toxicities including mucositis, xerostomia, Dysgeusia, dysphagia, nausea, and vomiting, the rate of malnutrition in these patients reaches 44-88% during treatment.

Several methods to improve nutritional status are commonly employed during chemoradiation. One common intervention is oral nutritional supplementation with commercially-available calorie-dense shakes like Boost® and Ensure®. Importantly, compliance with oral nutritional supplementation is challenging due to taste fatigue and treatment-related sequelae. Another commonly used intervention is the routine use of nutritional counseling, which has been shown, with or without oral nutritional supplementation, to have a positive impact during radiation and have a durable impact on QOL. Lastly, gastrostomy tube (G-tube) placement for enteral feedings is a third, and invasive, method for nutritional maintenance. While reliable for enhancing nutrition, long-term swallowing dysfunction may increase when patients rely on G-tube feedings for nutrition during chemoradiation, leading to higher rates of permanent G-tube dependence.

While several prospective studies have evaluated the value of oral supplementation during radiation alone for head and neck cancer, few studies evaluate this in the setting of concurrent *chemoradiation*, where side effects are more severe. These studies were also largely conducted in an era prior to modern intensity modulated radiotherapy (IMRT) for head and neck cancer, which has improved short-term and long-term toxicities like xerostomia and dysphagia, which can affect nutritional intake. Even with these improvements in radiotherapy delivery, a recent multi-institutional study of patients with oropharyngeal cancer revealed that 82% of patients receiving concurrent chemoradiation with IMRT had a G-tube inserted (about half in the therapeutic, rather than prophylactic, setting). Thus, there is ample opportunity to improve and evaluate the utility of structured oral supplementation with IMRT in patients with locally advanced disease necessitating chemoradiation.

Soylent™ is a novel oral nutritional supplement designed to be a complete meal replacement agent that is widely available to the general public, including through Amazon.com. In contrast to more commonly available oral supplements, it contains no sugar and is formulated to reduce taste fatigue, which may improve compliance in patients with head and neck cancer. Therefore, we hypothesize that complete nutritional replacement by Soylent™ triggered by 5% weight loss may be able to minimize further weight loss and improve nutritional status so as to reduce the therapeutic G-tube rate as compared to standard chemoradiation and supportive care at our institution. G-tube insertion will be recommended at 10% weight loss. Improved nutritional status from Soylent™ supplementation may improve toxicity, QOL, clinical outcomes, and may be associated with biomarkers predictive of treatment response or prognostic for cancer-related outcomes.

**PRIMARY OBJECTIVE (S):**

- (1) To determine the compliance rate of Soylent™ oral nutritional replacement
- (2) To determine the therapeutic G-tube placement rate (G-tube placement from the 1st day of chemoradiation up to 4 weeks following treatment)

**SECONDARY OBJECTIVE (S):**

- (1) To determine weight loss and body mass index (BMI) changes during and following treatment
- (2) To determine the change in nutritional and metabolic biomarkers during treatment
- (3) To determine physician-reported acute and late toxicities during and following treatment
- (4) To determine patient-reported quality of life during and following treatment
- (5) To determine clinical outcomes from treatment

**PRIMARY ENDPOINT (S):**

- (1) Compliance rate of oral nutritional supplementation
- (2) Therapeutic G-tube placement rate

**SECONDARY ENDPOINT (S):**

- (1) Weight loss
- (2) Body mass index (BMI)
- (3) Treatment breaks
- (4) Timing and duration of G-tube placement
- (5) Serum HPV DNA, pre-albumin, albumin, C-reactive protein (CRP), interleukin-6 (IL-6), tumor necrosis factor- $\alpha$  (TNF- $\alpha$ ), Vitamin A, Vitamin C, Vitamin D, tryptophan, kynurenine, leptin, and adiponectin, complete metabolic panel, and complete blood count
- (6) Radiosensitivity germ-line biomarker panel
- (7) Physician-reported acute and late toxicities according to the CTCAE version 4.0
- (8) Patient-reported quality of life according to the University of Washington and Functional Assessment of Cancer Therapy questionnaires
- (9) Local/Locoregional control
- (10) Distant metastasis-free survival
- (11) Overall survival

**STUDY DESIGN:**

Single arm, phase II prospective study to evaluate Soylent™ oral nutritional supplementation for compliance rate and impact on therapeutic G-tube rate, as well as its potential effect on nutrition, quality of life, and clinical outcomes with its use during chemoradiation in the definitive or adjuvant setting for head and neck cancer.

**NUMBER OF PATIENTS:**

60

**ELIGIBILITY CRITERIA:**

- Documented locally advanced head and neck malignancies for which concurrent chemoradiation has been recommended for definitive or adjuvant treatment

No history of prior radiotherapy to the head and neck; however, if previous treatment was superficial skin radiotherapy without regional lymph node treatment this will be allowed.

- Age  $\geq 18$  years
- Karnofsky Performance Status (KPS)  $\geq 70$
- Body mass index  $\geq 18\text{kg/m}^2$
- No evidence of distant metastatic disease (M1 disease)
- No G-tube placement prior to initiation of chemoradiation
- Eligible to undergo concurrent chemotherapy as determined by treating medical oncologist
- If a woman is of childbearing potential, a negative urine pregnancy test must be documented prior to proceeding with chemoradiation. Women of childbearing potential must agree to use adequate contraception (hormonal or barrier method of birth control; or abstinence) for at least 4 weeks after study treatment
- Ability to understand and willingness to sign a written informed consent
- Able to tolerate the taste of the oral nutritional supplement Soylent™ at the time of screening.
- Able and willing to participate in the Swallow Preservation Program at the Speech Pathology Clinic
- No evidence of clinically significant swallowing dysfunction by history or physical exam at time of radiation oncology consultation

**INTERVENTION AND MODE OF DELIVERY:**

Intervention is a commercially-available oral nutrition supplement. It will be provided by the study team to patients who are enrolled when their weight loss exceeds 5% from baseline. Patients will drink the supplements for nutrition during their meal times as directed by their clinical dietitian during and up to 1 month following chemoradiation. Patients will be recommended for Soylent™ supplementation as their only means of nutrition during the intervention period.

**DURATION OF INTERVENTION AND EVALUATION:**

Nutritional supplementation will take place if weight loss exceeds 5% from the baseline weight taken at study enrollment during concurrent chemoradiation. This is expected to occur in approximately 90% of patients undergoing chemoradiation from our institutional historical control data. Nutritional supplementation may continue until the month following completion of chemoradiation (up to approximately 3 month's total). Patients will be evaluated weekly by the study site's clinical dietitian and clinical staff to assess weight changes as is done for all patients undergoing chemoradiation to the head and neck. Patients will remove their shoes, items from their pockets, and any coats or sweaters. The dietitian and study staff will also determine the amount of supplementation utilized and assess the need of a G-tube during chemoradiation. G-tube placement will be recommended if a patient reaches 10% weight loss and/or is not meeting nutritional requirements as assessed by a dietitian. Patients will be required to be in a swallow preservation program with the Speech Pathology Clinic for minimizing dysphagia and aspiration surveillance. Clinical nutritional follow-up will continue as long as the patient is recommended to have nutritional supplementation. Weight measurements will be routinely taken at every follow-up visit. Blood/cheek swab sample collection (whenever feasible) for future analysis may occur at baseline (prior to treatment), at the conclusion of treatment (last week of chemoradiation), and at the 3-month follow-up visit. The University of Washington Quality of Life (UW-QOL) and Functional Assessment of Cancer Therapy Head & Neck (FACT-HN) questionnaires will be used

to assess QOL prior to beginning chemoradiation and at every routine follow-up after completing chemoradiation. Routine clinical follow-up will last for a minimum of 2 years.

## **STATISTICAL METHODS:**

### **SAMPLE SIZE JUSTIFICATION:**

Phase II: This study is designed to examine compliance and efficacy. That is, whether patients who require oral supplementation with Soylent™ continue using the supplement during treatment as directed ( $\geq 50\%$  of the time), and whether therapeutic G-tube rates are reduced by 33% with the utilization of oral nutritional supplementation with Soylent™ compared to our modern cohort of institutional historical control patients (treated from 2015-2016) who had received chemoradiation for head and neck cancer with standard nutritional counseling at our institution. One primary endpoint is to ensure compliance with Soylent™ nutritional supplementation during concurrent chemoradiation. For feasibility of using this meal replacement, we set a goal of more than 50% of patients should continue 50% of recommended daily Soylent intake. A therapeutic G-tube placement rate 33% lower than institutional historical control data is the second primary endpoint for this study. Our historical control data notes a 32% G-tube rate for chemoradiation patients, and we hypothesize reduction in g-tube placement to 20% of our patient population. If, conversely, a 25% higher rate of therapeutic G-tube placement occurs (equating to a 40% G-tube placement rate), study stoppage at an interim analysis period following treatment of 30 patients will be triggered. A sample size of 60 patients achieves 80% power to detect a 33% reduction in G-tube placement rate when comparing to historical control patients (i.e. 20% vs 32%), using a one-sided one-sample exact Binomial test, at a 0.10 significance level.

### **FUNDING, REGULATORY, AND FEASIBILITY ISSUES:**

The UCLA Department of Radiation Oncology has the capability, equipment, and expertise to provide oral supplementation, evaluate nutritional status, weight changes, and the need for a therapeutic G-tube during treatment. Clinical and radiographic follow-up will be performed per standard of care with blood samples and questionnaires issued per study protocol. Study associated costs outside of standard of care will be covered by the Department of Radiation Oncology.

### **PATIENT ACCEPTABILITY/ETHICS AND CONSENT ISSUES:**

Only patients able to give informed consent will be eligible for the study.

## SCHEMA

[figure not shown]

## **1.0 OBJECTIVES**

### **1.1 Primary objectives**

- 1.1.1 To determine the compliance rate of oral nutritional replacement with Soylent™
- 1.1.2 To determine the overall therapeutic G-tube placement rate (G-tube placement from the 1st day of chemoradiation up to 4 weeks following treatment)

### **1.2 Secondary objectives**

- 1.2.1 To determine weight loss and body mass index (BMI) changes during and following treatment
- 1.2.2 To determine the change in nutritional and metabolic biomarkers during and following treatment
- 1.2.3 To determine physician-reported acute and late toxicities during and following treatment
- 1.2.4 To determine patient-reported quality of life during and following treatment
- 1.2.5 To determine clinical outcomes from treatment

## **2.0 BACKGROUND**

Maintaining adequate nutrition to minimize weight loss during concurrent chemoradiotherapy for head and neck cancer is important for treatment adherence, treatment-related complications, quality of life (QOL), and even potentially clinical outcomes like death. However, chemoradiation usually results in multiple acute toxicities which make maintaining adequate nutritional intake challenging, including mucositis, xerostomia, dysgeusia, dysphagia, nausea, and vomiting. Therefore, avoiding malnutrition can be difficult, especially given that some patients (up to 52%) already have evidence of malnutrition prior to treatment commencing. Once on treatment, up to 88% of patients may have evidence of malnutrition.

Several methods to improve nutritional status are commonly employed during chemoradiation. One common intervention is oral nutritional supplementation with commercially-available shakes like Boost® and Ensure®, often initiated by clinicians early in treatment. A study of 23 patients randomized to either radiation alone or radiation with oral supplementation noted that all patients receiving nutritional supplementation had an increase in body weight, while 58% of the radiation alone group had weight loss. Additionally, no radiation treatment breaks were needed in the oral supplementation group, while 5/12 patients in the radiation alone group needed treatment breaks due to severe mucositis or poor performance status. Therefore, while a small study, oral supplementation appeared to benefit patients from a nutritional and toxicity perspective. Another prospective study of 50 patients treated by definitive radiation for head and neck cancer randomized patients to oral supplementation with Sustacal™ for 10 weeks or no supplementation. Notably, in this study patients having concurrent chemotherapy were excluded. The results of this study showed that although total protein and total calorie intake were increased in the supplemental group, equal levels of weight loss occurred. Furthermore, no differences in treatment response, complications, or survival were seen. Notably, only 67% of men and 56% of women consumed the recommended volume of supplementation (which contained 960-1080 kcal/day). Indeed, compliance with oral nutritional supplementation is challenging, both due to taste fatigue and treatment-related side effects. Even in other cancer sites, patient compliance with dietary interventions could be further optimized, with rates ranging from 47-69% in several studies.

Another commonly used intervention is the use of nutritional counseling, often in combination with oral nutritional supplementation. Nutritional counseling with or without oral supplementation has been shown to have a significant impact during (chemo) radiation and actually have a durable impact on QOL. One prospective, single-arm study of 21 patients noted relatively low levels of acute chemoradiation toxicity (33.3% with grade 3 mucositis) and nutritional decline with nutritional counseling and oral nutritional supplementation. A randomized study evaluating 75 head and neck cancer patients undergoing chemoradiation or radiation alone had 3 arms: dietary counseling with regular foods, usual diet with supplementation, and usual diet alone. The results showed significantly better oral intake and reduced incidence/severity of acute toxicities with dietary counseling as compared to either the usual diet with supplementation or usual diet alone.

Gastrostomy tube (G-tube) placement for enteral feedings is a third, and most invasive, method for nutritional maintenance in patients. This intervention is often recommended due to a contraindication for oral feeding like a high aspiration risk or patient refusal of adequate oral intake. Early G-tube insertion if it is in the best medical judgement by the treating physicians may be done prior to the 10% weight loss.

Early G-tube placement has been associated with reductions in weight loss, hospitalization from nutritional deficits, and persistent weight loss following treatment. While this is the most reliable way to enforce nutrition, long-term swallowing outcomes appear to suffer when patients do not swallow food during chemoradiation and instead rely upon G-tube feedings. Of note, G-tube dependence has been loosely associated with decreased survival metrics. Alternatively, nasogastric tube (NG-tube) feedings may promote a faster return to oral nutrition, but are generally not preferred given the significant patient discomfort and emotional distress associated with NG tubes. No survival differences have been shown by using prophylactic versus therapeutic (reactive) G-tube interventions to optimize nutritional status.

Important to note, many of the above randomized studies were performed without the use of concurrent chemotherapy. Also, these previous studies evaluating oral supplementation were largely conducted in an era prior to modern intensity modulated radiotherapy (IMRT) for head and neck cancer, which has improved short-term and long-term toxicities like xerostomia and dysphagia, which can in turn affect nutritional intake. A recent multi-institutional study of patients receiving definitive IMRT for oropharyngeal cancer revealed 63% had a G-tube placed, with 48% having reactive (vs. prophylactic) G-tube placement. Importantly, 82% of patients having concurrent chemoradiation had a G-tube inserted. Thus, there is an opportunity to evaluate the utility of oral supplementation with IMRT in patients with locally advanced disease necessitating chemoradiation. Additionally, patient-reported QOL has, to our knowledge, never been evaluated using an oral supplement intervention for chemoradiation, although it has been reported in patients receiving radiation alone.

Multiple studies have noted associations between metabolic and nutritional biomarkers with the risk of malignancy, treatment-related toxicities, and cancer-related outcomes. Serum albumin

level is a marker which correlates with mortality in head and neck cancer patients. Pre-albumin is a more sensitive marker than albumin in head and neck cancer patients undergoing RT. Chemoradiation has been associated with changes in BUN, creatinine, bicarbonate, magnesium, albumin, sodium, and potassium levels. C-reactive protein appears to increase during chemoradiation. Vitamins C and E appear to mitigate RT-induced xerostomia following treatment for head and neck cancer. Mixed evidence has been reported regarding the association of vitamin D levels with head and neck cancer outcomes.

Targeted supplementation to increase clinically-relevant biomarkers have been explored in head and neck cancer. One small study utilized omega-3 fatty acid and arginine-enhanced supplementation in surgical head and neck cancer patients, which resulted in improved blood protein concentrations, lymphocyte levels, and weight. Another study with arginine-enhanced supplementation in post-operative head and neck cancer patients showed significantly decreased fistula formation. In a third small study where patients with head and neck cancer underwent chemoradiation or palliative chemotherapy, patients randomized to a supplement regimen with added omega-3 fatty acids, micronutrients, and probiotics versus a control supplement. This showed significantly improved weight, higher serum albumin, and higher pre-albumin.

Molecular biomarkers may also be helpful in predicting treatment response and prognosis in head and neck cancers. HPV is known to predict treatment response and prognosis in HPV-associated head and neck cancers of the oropharynx. In head and neck cancers of the oral cavity, saliva is preferentially enriched for tumor DNA, while for other subsites plasma DNA is preferentially enriched. Associating nutritional status to HPV DNA levels may be revealing.

SoylentTM is a novel, widely available, oral nutritional supplement designed to be a complete meal replacement agent. In contrast to commonly utilized oral supplement preparations, it does not rely on sugar to provide caloric intake, and it has a taste designed to reduce taste fatigue, which may improve compliance. Therefore, we hypothesize that SoylentTM would have a compliance rate which would make its use feasible for patients undergoing head and neck cancer chemoradiation. Also, we hypothesize that complete meal replacement starting at 5% weight loss, rather than ad hoc supplementation, may be able to minimize weight loss, improve nutritional status, and reduce the therapeutic G-tube rate significantly better than traditional methods in a modern cohort of head and neck cancer patients treated with chemoradiation. Furthermore, SoylentTM supplementation may affect nutritional, metabolic, and molecular biomarkers predictive for treatment response or for cancer-related outcomes. Lastly, we hypothesize that SoylentTM supplementation may impact toxicity, QOL, and cancer-related outcomes.

### **3.0 PATIENT SELECTION**

#### **3.1 Conditions for patient eligibility**

3.1.1 Documented locally advanced head and neck malignancies for which concurrent chemoradiation has been recommended for definitive or adjuvant treatment

3.1.2 No history of prior radiotherapy to the head and neck. However, if previous treatment was superficial skin radiotherapy without regional lymph node treatment this will be allowed.

##### **3.1.2.1**

3.1.3 Age  $\geq 18$  years

3.1.4 Karnofsky Performance Status (KPS)  $\geq 70$

3.1.5 Body mass index  $\geq 18$  kg/m^2

3.1.6 No evidence of distant metastatic disease (M1 disease)

3.1.7 No G-tube placement prior to initiation of chemoradiation

3.1.8 Eligible to undergo concurrent chemotherapy as determined by treating medical oncologist

3.1.9 If a woman is of childbearing potential, a negative urine pregnancy test must be documented prior to proceeding with chemoradiation. Women of childbearing potential must agree to use adequate contraception (hormonal or barrier method of birth control; or abstinence) for at least 4 weeks after study treatment.

3.1.10 Ability to understand and willingness to sign a written informed consent

3.1.11 Able to tolerate the taste of one of the flavors of the oral nutritional supplement Soylent™

3.1.12 Able and willing to participate in the Swallow Preservation Program at the Speech Pathology Clinic

3.1.13 No evidence of clinically significant swallowing dysfunction by history or physical exam at time of radiation oncology consultation

#### **3.2 Conditions for patient ineligibility**

3.2.1 Patients who have previously received therapeutic radiation therapy to the head and neck except for superficial skin radiotherapy is allowed.

3.2.2 Patients who had G-tube placement due to concern for aspiration or due to severe malnutrition in advance of chemoradiation

3.2.3 Patients underweight in advance of chemoradiation (BMI  $< 18$  kg/m^2)

3.2.4 Patients who refuse to use Soylent™ oral nutritional supplementation due to its taste or other patient preference reasons

3.2.5 Patients with allergies to any of the ingredients contained in the nutritional supplement

3.2.6 Pregnant women, or women of childbearing potential who are sexually active and not willing/able to use medically acceptable forms of contraception for the entire study period and for up to 4 weeks after the study treatment.

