3.2.7 Refusal to sign the informed consent

3.2.8 Refusal to participate in the Swallow Preservation Program prior to start of Soylent if applicable.

3.2.9 Evidence of clinically significant swallowing dysfunction by history or physical exam at time of radiation oncology consultation

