### **4.2 Registration Process**

Informed consent form will be given to the patient for review. Consent will be obtained after a clear and thorough discussion between the patient and the study investigator in clinic. When practical and in the best interest of the subject, the consent discussion may occur by telephone/telemedicine. The IRB-approved informed consent document may be sent to the subject electronically to be signed and returned electronically to the investigator for counter-signature. To register a patient, the research coordinator will obtain or complete: (1) documentation of locally advanced head and neck cancer for which chemoradiation has been recommended (2) successful taste test of Soylent™ nutritional supplement (3) signed informed consent form; (4) signed HIPAA authorization form.

Prior to confirmation of eligibility and enrollment in the study, the following will be obtained anytime in advance of beginning chemoradiation: (1) Total amount of blood samples that can potentially be collected 82.5 mL (27.5 mL at each draw), (2) cheek swabs sample, (3) quality of life assessments.

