## 10. STATISTICAL CONSIDERATIONS

### 10.1 Study Endpoints

#### 10.1.1 Sample Size and Power Consideration

This is a single arm, phase II prospective study to evaluate Soylent™ oral nutritional supplementation for compliance rate and potential impact on therapeutic G-tube rate, nutrition, quality of life, and clinical outcomes with its use during and immediately following chemoradiation in the definitive or adjuvant setting for head and neck cancer. The primary endpoints are compliance rate of Soylent™ oral nutrition supplementation and therapeutic G-tube rate. We plan to enroll 60 patients.

One primary endpoint is to ensure compliance with Soylent™ nutritional supplementation in patients undergoing concurrent chemoradiation. For feasibility in using this supplement for head and neck cancer patients, a goal of more than 50% of patients should continue to use this supplement (to at least 50% of recommended quantities) throughout treatment once initiated.

A therapeutic G-tube placement rate 33% lower than institutional historical control data is the second primary endpoint for this study. Our historical control data notes a 32% G-tube rate for chemoradiation patients, so the goal endpoint is 20%. If, conversely, a 25% higher rate of therapeutic G-tube placement occurs (equating to a 40% G-tube placement rate), this should trigger study stoppage. A sample size of 60 patients achieves 80% power to detect a 33% reduction in G-tube placement rate when comparing to historical control patients (i.e. 20% vs 32%), using a one-sided one-sample exact Binomial test, at a 0.10 significance level.

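### The compliance endpoint does not say whether a patient who reaches the 5% trigger and declines to start Soylent is counted

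*Protocol*

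**What the plan says.** **Population and goal.** The synopsis (Sample size justification) says the study examines "whether patients who require oral supplementation with Soylent™ continue using the supplement during treatment as directed", and then: "we set a goal of more than 50% of patients should continue 50% of recommended daily Soylent intake". Section 10.1.1 restates the goal: more than half of patients "should continue to use this supplement (to at least 50% of recommended quantities) throughout treatment once initiated".

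**Definition.** Section 5.4 defines compliance as continuing with at least half of the Soylent that the dietitian recommends. It names as non-compliant a patient who stops altogether and does not resume while the recommendation stands, and it treats refusal to resume in the same way. It exempts stopping when the patient holds weight on regular food, goes on to a G-tube or shows aspiration, and it allows other nutrition alongside Soylent. Declining to start is neither named as non-compliance nor exempted.

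**Analysis.** Section 10.2.1 gives a compliance rate with a 95% exact confidence interval and names no denominator.

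**Taste at entry.** The synopsis requires patients to be "Able to tolerate the taste of the oral nutritional supplement Soylent™ at the time of screening". Section 3.1.11 has "Able to tolerate the taste of one of the flavors of the oral nutritional supplement Soylent™", without a date. Section 4.2 requires a "successful taste test of Soylent™ nutritional supplement" before registration. Exclusion 3.2.4, also undated, reads "Patients who refuse to use Soylent™ oral nutritional supplementation due to its taste or other patient preference reasons".

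**The concern.** Soylent is not given at enrolment. Under section 5.4 it begins once 5% of body weight has been lost during chemoradiation, so there is a gap between the taste test at registration and the first recommended bottle. The synopsis and section 2.0 both say that compliance with oral supplements is hard because of taste fatigue and treatment side effects. Some patients who passed the taste test may therefore decline at the trigger, and declining outright is the most complete form of non-compliance.

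The wording leaves it open whether such a patient counts. Needing Soylent is a property of everyone who reaches the trigger; use after initiation is a property of starters only. If the rate is computed among starters, the first primary endpoint loses the patients for whom the intervention failed earliest, and the choice between the two readings could be made after the data are known.

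**Working it through.** **Inputs**
- Planned enrolment: 60 (section 10.1.1).
- Share expected to reach 5% loss: about 90% (synopsis, Duration of intervention and evaluation).
- Goal: more than 50% of patients compliant (synopsis; section 10.1.1).
- Number declining at the trigger: not given in the protocol. The values of k below are assumptions, and none of these decliners is taken to fall under a section 5.4 exemption.

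**The plan's own figure.** The only power statement concerns the G-tube endpoint (20% against 32%, one-sided exact binomial, alpha 0.10, n = 60, 80% power). The rejection region is 14 or fewer placements, with P(X ≤ 14 | 60, 0.32) = 0.0943 and P(X ≤ 14 | 60, 0.20) = 0.7935. That agrees with the stated 80% to within a point and is untouched by this issue. The compliance endpoint has no power or sample-size figure to reproduce.

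**Patients at the trigger.** T = 0.90 × 60 = 54.

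**Two rates from the same data.** Let x be the number compliant and k the number who decline to start.
- All who reach the trigger: x / T.
- Starters only: x / (T − k).

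For x > 0 and k > 0 the second always exceeds the first, so the direction is fixed.

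| k (assumed) | x | x / 54 | x / (54 − k) |
|---|---|---|---|
| 1 | 27 | 50.0%, missed | 27/53 = 50.9%, met |
| 5 | 27 | 50.0%, missed | 27/49 = 55.1%, met |
| 6 | 25 | 46.3%, missed | 25/48 = 52.1%, met |
| 10 | 23 | 42.6%, missed | 23/44 = 52.3%, met |

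**Fewest compliant patients that meet the goal** (smallest x with x / (54 − k) > 0.5)
- k = 0: 28/54 = 51.9%.
- k = 3: 26/51 = 51.0%, which is 26/54 = 48.1% of those at the trigger.
- k = 5: 25/49 = 51.0%, which is 25/54 = 46.3%.
- k = 11: 22/43 = 51.2%, which is 22/54 = 40.7%.

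**Stated as a proportion.** If 55% of starters comply, the rate among all who reach the trigger is 0.55 × (1 − refusal): 49.5% at 10% refusal, 44.0% at 20% and 38.5% at 30%.

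**Precision.** The exact 95% interval is 36.1% to 63.9% for 27/54 and 40.2% to 69.3% for 27/49. The intervals overlap widely. What changes is the point estimate, which is what I assume is compared with the 50% goal, since section 10.2.1 gives no test for compliance.

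**The case against.** **Section 5.4 may already settle it.** Compliance is measured against the recommended amount. A patient who takes none of it does not reach half and is not among the exemptions. This stands as a legitimate reading. It is not the only one: the definition speaks of continuing, both named failures presuppose a start, and 10.1.1 speaks of use after initiation.

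**The phrase in 10.1.1 may describe a period, not a population.** It can be read as saying over what time use is judged, and the subject of the sentence is simply patients. That is fair, and it is why the text leaves the matter open and does not positively exclude decliners.

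**Analysis sets are usually left to the SAP.** A missing denominator in 10.2.1 would not by itself be a finding. Here, however, the protocol describes the population of a primary endpoint in two ways that give different rates.

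**The examples are chosen near 50%.** True. Far from 50% the choice of denominator shifts the estimate without changing the conclusion.

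**A stronger inference that the protocol does not support.** A reader might infer that undated exclusion 3.2.4 lets an enrolled patient who refuses at the trigger be reclassified as ineligible and so removed from the endpoint. Exclusion 3.2.8 in the same list, "Refusal to participate in the Swallow Preservation Program prior to start of Soylent if applicable", refers to a moment after enrolment and makes the inference tempting. But 3.2.4 is an entry criterion, the synopsis dates the taste criterion at screening, section 4.2 puts the taste test before registration, and section 10.5 handles removal after enrolment without invoking 3.2.4. Nothing in the protocol reclassifies an enrolled patient at the 5% trigger.

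**Conclusion.** The point holds as an inconsistency in the population of the first primary endpoint. The protocol does not say that decliners leave the compliance rate; it permits that reading alongside one in which they count as non-compliant. The starters-only reading can only raise the rate. With 54 patients at the trigger, the goal needs 28 compliant patients if all count, but 25 if five decliners are dropped, and a single decliner decides the matter when 27 comply.

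These sizes rest on the protocol's approximate 90%, on assumed numbers of decliners, on no decliner being exempt, and on judging the goal by the point estimate. The G-tube endpoint and its power are unaffected. This is worth correcting because it bears on a primary conclusion and costs almost nothing, but it is not a defect that undermines the design.

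**What to change.** - **Section 10.1.1:** define the compliance denominator as all enrolled patients who reach 5% weight loss and are recommended Soylent, and drop the wording that ties the goal to initiation. This brings it into line with the synopsis.
- **Section 5.4:** state that a patient who is recommended Soylent and declines to start counts as non-compliant, outside the exemptions already listed there.
- **Tidying only:** add that 3.1.11 and 3.2.4 are assessed at screening, to match the synopsis and section 4.2. Reporting how many patients fail the taste test is optional; it would show that the rate applies to people who already accept the taste.

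The cost is a few sentences, with no added patients, visits or procedures. The reported compliance rate may be slightly less favourable.
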